### Timeline

This study is planned to occur over 3 years, with a recruitment window of 18 months to recruit the full sample of 370 participants. The proposed timeline includes 20% of the sample being recruited in Year 1 (2022); 60% in Year 2 (2023); and the final 20% in Year 3 (2024), with the remainder of Year 3 devoted to collection of follow-up data and analysis.

### Measures

Table 2 outlines the efficacy outcomes that will be assessed using a battery of validated self-report measures at baseline, post-intervention (primary endpoint), 3-month and 6-month follow-ups, supplemented with website usage data and patient health service use data obtained via data linkage of government databases (‘Services Australia’). Figure 3 outlines the schedule of assessments.

#### Sample characteristics

The demographic, clinical and treatment characteristics will be captured via self-report and confirmed via chart review (where available), and are outlined in Table 2.

#### Primary outcome: mental QOL

Mental QOL will be measured using the EORTC QLQ C-30 emotional functioning subscale [33]. Total scores range from 0 to 100, with higher scores indicating better functioning. QOL has been selected as the primary outcome as it is one of two priority outcomes for MBC nominated by Cancer Australia [2], and has not had sufficient focus in earlier trials [34]. Furthermore, it is a meaningful outcome to patients [2], correlates well with other clinical outcomes and is demonstrated to be sensitive to change [35, 36].

#### Secondary outcomes

Secondary outcome measures assessing QOL, psychosocial and health-economic outcomes, and covariates are summarised in Table 2.

#### User satisfaction

User satisfaction will be assessed using single Likert-style items in the follow-up questionnaire asking participants how helpful they found aspects of the program, and how confident they felt they could apply the program to their everyday life, and through qualitative interviews.

**Table 2 Tab2:** Measures of Secondary Outcomes, Sample Characteristics, and Baseline Covariates

Domain/Measure	Description
Secondary Outcomes	
QOL	Other dimensions of quality of life will be measured by the EORTC QLQ-C30 subscales (global QOL; physical, social, role, cognitive functioning; physical symptoms) [33].
Distress	The 21-item Depression Anxiety Stress Scale [37]. Assesses anxiety, depression and stress over the previous week; total distress score will be used. The total scale score of the 17-item Post-traumatic Stress Scale-Self-Report (PSS-SR) will be used to measure cancer-specific distress [38]. Items measure symptoms experienced over the past week, rated on a 4-point scale (0 = not at all to 4 = almost always), and anchored to cancer diagnosis as the stressor. Higher scores indicate higher cancer-specific distress
Fear of Progression	The English-version of the 12-item Fear of Progression Questionnaire short form measures levels of anxiety regarding cancer progressing on a five-point Likert scale from 1 (‘never’) to 5 (‘very often’) [39].
Unmet needs	34-item Supportive Care Needs Survey – Short Form [40]. Measures perceived psychosocial, information, physical/activity of daily living, patient care and sexuality needs.
Cost utility	The EuroQol 5 dimensions 5 level (EQ-5D-5L) is a generic preference-based measure [41]. Based on Australian-specific algorithms ranging from − 0.281 to 1, utility scores will be converted into quality adjusted life years (QALYs) required for cost-utility analysis.
Participant Characteristics and Covariates (collected at baseline only)	
Socio-demographic characteristics	Age, marital status, sexual orientation, children, occupational status, annual gross income, educational attainment level, area of residence/postcode, ethnicity.
Medical characteristics (To be assessed via self-report and confirmed via hospital chart review where available)	Date of MBC diagnosis, date of previous BC diagnosis (if applicable), tumour type (hormone status, site of progression), treatments received or planned (surgery, chemotherapy, radiotherapy, hormonal therapy, other), other health conditions, number of prescription medications (to calculate comorbidity index: Rx-Risk score [42], and other support-services accessed (including psychology).
Social support	The Medical Outcome Study Social Support Survey yields a total-scale score and four subscales: emotional/informational, tangible, affectionate, and positive social interactions [43].
Objective Utilisation Data: Website Adherence and Health Service Utilisation	
Intervention adherence	Number of visits, session duration, number of modules completed, pages viewed, and worksheets completed [35].
Services Australia-reported health service use and costs	Medicare Benefits Schedule (MBS) data will be accessed to determine the number and costs of primary care visits, medical consultations, treatments, investigations, and out-of-hospital visits; Pharmaceutical Benefits Scheme (PBS) data to estimate quantity and costs of pharmaceuticals.
Public-hospital costing data (For South Australian recruitment site only)	Centralised costing data in public hospitals (Australian Refined Diagnosis Related Groups (AR-DRGs) will be accessed for determining the number and costs of public hospital inpatient episodes. While this only covers public health sector costs and is not available for participants who self-refer this limitation will apply equally to both groups, due to randomisation.

**Fig. 3 Fig3:**
[figure not shown]
Schedule of enrolment, interventions, and assessments

### Trial oversight

The trial has four levels of oversight. Routine *operational oversight* of the trial is managed by the Coordinating Centre, comprised of principle coordinating investigators (LB, EK, BKo) and affiliated students working on the project. Bi-monthly Project Management Group meetings, comprised of coordinating centre members and three named consumer investigators, oversee *governance and recruitment* aspects of the trial. The Steering Committee, comprised of all investigators, associate investigators, consumer representatives and site coordinators, meet bi-annually at a minimum to provide *strategic oversight* and broader project management and planning. Finally, *data management* for the trial is managed by the Data Management Team, comprised of coordinating centre members, biostatistician (RW) and health economist (BKa). A separate data monitoring committee is not required, due to the automated and self-report nature of the data. Trial conduct will not be externally audited; the trial oversight committees will conduct regular internal audits.

### Safety reporting

Participants will be closely monitored throughout the study by the Coordinating Centre through questionnaires and feedback comments delivered via the website. Participants are free to withdraw from the trial at any time. Reasons for withdrawal will be documented (where provided), and withdrawing participants will still be offered the opportunity to participate in a qualitative interview substudy. Significant adverse effects (e.g., emotional, psychological, and physical) will be monitored and reported to the Southern Adelaide Clinical Human Research Ethics Committee (SAC-HREC).

### Data management

Only Coordinating Centre investigators and web developers will have administrative access to the website and data. All data will be kept in a re-identifiable form using a patient identification code. Electronic data will be stored on secure Flinders University password-protected servers. Data will be used for research publications in academic journals and presentation at scientific meetings and conferences. No data linkage or secondary use of data is planned or anticipated.

### Statistical methods

#### Sample size and justification

The sample size calculation is based on a repeated measures ANCOVA approach, which takes into account the within-subject correlation across measures, using STATA’s “sampsi” routine and our primary outcome of MQOL. Assuming a between-subject SD of 20 points, 1 baseline measure, and 3 post-baseline measurements per subject (post-treatment, 3-months and 6-months) and a within-subject QOL rho = 0.6, *n* = 147 subjects per group will provide 80% power to detect a clinically meaningful difference in MQOL between treatments of 4 points. Based on attrition rates observed in low-intensity MBC interventions (range 4-20%) and our pilot data to date, we will recruit and enrol 185 subjects per group (total *n* = 370; 46 per recruitment site) to allow for 20% attrition. Based on our pilot data where 71% of eligible women consented, 530 women will be approached (equating to approximately 66 *approached* per recruitment site over the 18-month recruitment window, or 3 to 4 per month), to reach the final sample size of 370.

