**Methods:**

The multi-site randomised controlled trial (RCT) will enrol 370 Australian participants. Eligible participants are adult (18 years +) women diagnosed with MBC, with a life expectancy of 6 months or more, with sufficient English-language literacy to provide informed consent. Participants will be identified, screened and referred from one of 10 Australian sites, or via self-referral in response to advertisements. Participants complete four online questionnaires: prior to accessing their program (‘baseline’), 6 weeks later (‘post-intervention’), then 3 months and 6 months post-intervention. Consenting participants will be randomised to either *FMW-A* (intervention), or Breast Cancer Network Australia’s (BCNA) online/app resource *My Journey* (minimal intervention attention-control). This is a single-blind study, with randomisation computer-generated and stratified by site. *FMW-A* is a 6-module program addressing some of the most common issues experienced by women with MBC*,* with BCNA control resources integrated within the ‘resources’ section*.* All modules are immediately accessible, with an additional booster module released 10 weeks later. The primary outcome is mental QOL; statistical criteria for superiority is defined as a 4-point difference between groups at post-treatment. Secondary outcomes include other QOL domains, distress, fear of progression, health service use, intervention adherence, and user satisfaction.

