**Discussion:**

This will be the first adequately powered RCT of a self-directed online intervention for women with MBC. If efficacious, *FMW-A* will help address two national key priorities for management of MBC – enhancing QOL and reducing symptom burden. *FMW-A* has the potential to address unmet needs and overcome access barriers for this overlooked population, while reducing health system burden.

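### The stated 80% power is for the average of three follow-ups; at the declared primary endpoint, post-treatment alone, the same inputs give 57% to 67%

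*Protocol article*

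**What the plan says.** The section on sample size and justification uses a repeated measures ANCOVA calculation in Stata's sampsi, with an SD of 20 points and "1 baseline measure, and 3 post-baseline measurements per subject (post-treatment, 3-months and 6-months) and a within-subject QOL rho = 0.6". From these inputs it concludes that "147 subjects per group will provide 80% power to detect a clinically meaningful difference in MQOL between treatments of 4 points". Enrolment is then set at 185 per group to allow for 20% attrition.

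Other sections locate the primary comparison at one visit:

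- Under Measures, outcomes are collected "at baseline, post-intervention (primary endpoint), 3-month and 6-month follow-ups".
- In the Abstract (Methods), "statistical criteria for superiority is defined as a 4-point difference between groups at post-treatment".
- Under Hypotheses, the primary hypothesis concerns improvement from baseline to post-intervention. The 3- and 6-month visits enter only as evidence that the effect lasts.

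Under Primary analyses, a linear mixed model is planned with baseline as a covariate. It lists treatment and time as fixed main effects, and also describes a group-by-time test and linear contrasts at chosen time points. It does not say which test is primary.

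The Abstract (Discussion) states: "This will be the first adequately powered RCT of a self-directed online intervention for women with MBC".

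**The concern.** A repeated measures ANCOVA calculation with three post-baseline measurements gains precision by averaging them. That gain belongs to a treatment effect that is averaged over the three visits, or assumed equal at all of them. It does not carry over to the difference at one of the visits. The same 4 points appears in the power statement and in the post-treatment superiority criterion, so a reader will take the 80% to apply to post-treatment.

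If it does not, a non-significant post-treatment result would come from a trial described as adequately powered that had a substantial chance of missing its own target difference. The unresolved choice between the post-treatment contrast and the pooled effect would also leave room to choose between them after seeing the data.

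**Working it through.** **Inputs from the sample size section:** difference 4 points; SD 20 (variance 400); one baseline and three post-baseline measurements; a single correlation of 0.6, taken to hold between every pair of assessments; 147 analysable and 185 enrolled per group; 80% power.

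**Assumed:** two-sided alpha of 0.05. The article gives no alpha. Two-sided 5% reproduces 147, whereas one-sided 5% gives 116.

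**Formulas.** With one baseline and r follow-ups, the ANCOVA variance factor is

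f = [1 + (r − 1)ρ]/r − ρ²

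The number per group is n = 2(1.960 + 0.842)² × SD² × f / d². The standard error of the group difference is SE = √(2 × SD² × f / n). Power is Φ(d/SE − 1.960).

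**Step 1: reproduce the plan's figure (r = 3, average of the follow-ups).**

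- f = (1 + 2 × 0.6)/3 − 0.36 = 0.7333 − 0.36 = 0.3733
- n = 2 × 7.849 × 400 × 0.3733 / 16 = 146.5, rounded up to 147
- Power at 147 is 80.1%
- Attrition: 147/0.8 = 183.75, so 184 against the stated 185

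The plan's arithmetic is sound for this quantity. Variants that do not give 147 include ANCOVA with two follow-ups (173), three follow-ups without baseline adjustment (288) and change from baseline with three follow-ups (210).

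**Step 2: the same inputs at post-treatment alone (r = 1).**

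- f = 1 − 0.36 = 0.64
- n for 80% power = 2 × 7.849 × 400 × 0.64 / 16 = 251.2, so 252 per group
- At 147 per group: SE = √(512/147) = 1.866; power = Φ(4/1.866 − 1.960) = Φ(0.183) = 57.3% (57.0% with the noncentral t)
- At 185 per group: SE = √(512/185) = 1.664; power = Φ(4/1.664 − 1.960) = Φ(0.444) = 67.2%
- Difference detectable with 80% power = 2.802 × SE: 5.2 points at 147 and 4.7 points at 185

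**Step 3: can the mixed model recover the loss?** With a group-by-time term, complete data and equal correlations, the post-treatment contrast has variance 2 × SD² × (1 − ρ²)/n, the same as single-visit ANCOVA. Later visits add essentially nothing when the post-treatment value is observed. A generalised least squares check with 20% lost before post-treatment (148 per group left) gives 57.6% at post-treatment and 80.4% for the average. If loss is gradual and 173 per group are observed at post-treatment, SE = √(512/173) = 1.720 and power is 64%.

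**Step 4: sensitivity at 147 per group, post-treatment only.**

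| Correlation with baseline | Power for 4 points | n per group for 80% |
|---|---|---|
| 0.5 | 51% | 295 |
| 0.6 | 57% | 252 |
| 0.7 | 67% | 201 |
| 0.8 | 82% | 142 |

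A correlation near 0.8, well above the plan's 0.6, would be needed to reach 80%. A one-sided 5% test would give 69%, but then 147 would no longer be the number the method returns.

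**The case against.** The strongest reply rests on the Primary analyses section. Its sentence listing the fixed effects names treatment and time as main effects. If that is the whole fixed part of the model, the treatment coefficient is one common effect over the three follow-ups, which 147 per group does power at 80%. The primary objective and the definition of the primary outcome also carry no time point. On this reading the sample size is right and the references to post-treatment are loose wording.

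Part of this stands: the 57% to 67% applies to a post-treatment contrast, and the article never states outright which test from the model is primary. But the same section also plans a group-by-time test and contrasts at individual time points, and nowhere makes the pooled effect primary. The Abstract, the Hypotheses and the Measures section all point to post-treatment. If a common effect was intended, those three places contradict it, so the passages have to be reconciled either way.

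Two further points are fair. Alpha is inferred, not stated. And 57% supposes that the full 20% attrition has already occurred six weeks after enrolment, which the article does not say; the range up to 67% should be reported. With 185 enrolled per group and the plan's other inputs, no attrition pattern takes post-treatment power above 67%.

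**Conclusion.** The concern holds. Nothing is miscalculated in the 147; it answers a different question from the one declared primary. For a 4-point difference at post-treatment, power is 57% with 147 per group and at most 67% with all 185 observed, against the 80% claimed. This rests on the plan's SD of 20 and correlation of 0.6, an assumed two-sided 5% test, and a primary test made at post-treatment, as the Abstract, Hypotheses and Measures sections say. Over correlations of 0.5 to 0.7, power at 147 per group is 51% to 67%, so the conclusion does not depend on the exact value. The statement that the trial is adequately powered is not supported for the declared endpoint.

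**What to change.** Choose one of the following before any outcome data are seen.

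1. **Keep post-treatment as primary and restate the power.** Suggested wording: *For the post-treatment contrast (SD 20, correlation 0.6, two-sided 5%), 147 analysable participants per group give 57% power for 4 points and 80% power for 5.2 points; if all 185 per group are observed, the figures are 67% and 4.7 points.* Remove the claim of adequate power from the Abstract and state alpha explicitly. The cost is wording and a less favourable figure; no extra participants are needed.

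2. **Make the adjusted difference averaged over the three follow-ups the primary contrast**, which is what 147 per group powers. The Abstract, Hypotheses, Measures and Primary analyses sections must then all say so. This changes the primary question of a prospectively registered trial, so it must be checked against the registration and documented as an amendment. No extra participants are needed.

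3. **Re-size for 80% power at post-treatment:** 252 analysable per group, or 252/0.8 = 315 enrolled per group and 630 in total, against the planned 370. This is the only option that needs more participants.

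Option 1 is the least that is needed.

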### Primary analyses

Linear Mixed Models (LMM) will be employed following completion of data collection to examine the efficacy of the intervention, in line with the statistical methodology utilised in previous trials our group has published [27, 28]. Analysis will be by intention to treat, defined as all patients who register. LMM will be used to model all continuous outcomes while accounting for covariance between repeated measures on patients and adjusting for baseline measures, which improves precision of estimation of effects. These models will allow for comparing patterns of change over time by testing group by time interaction, and estimating and testing differences between groups at time points of interest via linear contrasts. Mixed models are valid for data that are missing completely at random and missing at random; patterns of missing data will be considered to assess potential missing data mechanisms. In the present study, the fixed main effects will be treatment condition (intervention, control), and time (post-treatment, 3-month, 6 month), with the baseline measure of the outcome entered as a covariate. A random subject effect will be entered into the model to allow the trajectory of each individual to differ by a constant elevation from the group trajectory. Between-group effect sizes and reliable change indices will be calculated to provide a measure of the magnitude and clinical significance of changes, respectively. No interim analysis is planned.

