### Hypotheses

Primary hypothesis:Intervention participants will report greater improvements in the primary outcome of mental QOL (MQOL) compared to minimal-intervention control participants from baseline to post-intervention, with effects sustained at 3- and 6-month follow-ups.

Secondary hypotheses:Intervention participants will report greater improvements from baseline to post-treatment in secondary well-being outcomes, i.e., physical, social, cognitive, role and global QOL domains; fear of progression; psychological distress; and unmet needs, compared to control participants, with effects sustained at 3- and 6-month follow-ups.Intervention participants will have lower health service utilisation and public hospital admissions (indicator of cost savings to the health service) over the 6-month follow-up period, compared to control participants.

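### The group-by-time test listed among the efficacy analyses does not measure improvement from baseline, and the primary decision should be tied to the post-intervention contrast

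*Protocol article*

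**What the plan says.** The Primary analyses section describes linear mixed models used to examine efficacy. It says they allow "comparing patterns of change over time by testing group by time interaction" and, in the same sentence, "estimating and testing differences between groups at time points of interest via linear contrasts". The fixed main effects are treatment condition and "time (post-treatment, 3-month, 6 month), with the baseline measure of the outcome entered as a covariate". A random subject effect is added to "allow the trajectory of each individual to differ by a constant elevation from the group trajectory", which is a random intercept.

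The primary hypothesis (Hypotheses) is a greater improvement in mental quality of life in the intervention group "from baseline to post-intervention, with effects sustained at 3- and 6-month follow-ups". The Abstract (Methods) states that "statistical criteria for superiority is defined as a 4-point difference between groups at post-treatment", and the Measures section also labels the post-intervention assessment as the primary endpoint. The sample size section bases 147 per group on a 4-point difference, with one baseline and three post-baseline measurements.

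Below, T1, T2 and T3 are the post-intervention, 3-month and 6-month assessments, as in the Study procedures and timeline section.

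**The concern.** A group-by-time interaction carries differential change from baseline only if baseline is one of the levels of time. Here it is not. A reader who connects the hypothesis, worded as improvement from baseline, to the interaction, worded as patterns of change, would look for the treatment effect in a term that does not contain it.

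The test also runs against the hypothesis. If the programme produces a benefit by T1 and holds it, the interaction is null; if the benefit fades, the interaction becomes more likely to be significant. An analysis that gave this test weight as evidence of efficacy could report no effect for a programme that worked as intended. The section lists the interaction, contrasts at unspecified times and a treatment main effect without saying which one decides, and these tests differ greatly in power.

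**Working it through.** **What the interaction estimates.** Write the model as outcome at time t = time effect + group effect + group-by-time effect + c × baseline + random intercept + error. The interaction is built from differences between times within a participant, such as T2 − T1. In such a difference both the baseline term and the random intercept cancel. What remains is the difference between groups in change after T1. If the adjusted group differences are d1, d2 and d3, the interaction is zero whenever d1 = d2 = d3, however large that common value is.

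**Inputs.** From the sample size section: difference 4, SD 20, correlation ρ = 0.6, one baseline and three post-baseline measures, n = 147 per group, 80% power. From Primary analyses: time levels T1 to T3, baseline as covariate, random intercept. Alpha is not stated. I assume two-sided 0.05, which reproduces 147; one-sided 0.05 would give 116.

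**Reproducing the plan's figure.** For the effect averaged over three post-baseline measures with baseline adjustment, the variance factor is

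f = (1 + 2 × 0.6)/3 − 0.6² = 0.7333 − 0.36 = 0.3733.

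The effective SD is 20 × √0.3733 = 12.22, and n = 2 × (1.960 + 0.842)² × 12.22² / 4² ≈ 147 per group. Power at 147 is 80.1%. Allowing for 20% attrition gives 147/0.8 = 183.75, so 184, against the stated 185. The plan's figure is reproduced, and it belongs to the averaged effect.

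**Contrast at T1 alone.** The factor is f = 1 − 0.6² = 0.64 and the effective SD is 16. The standard error at 147 per group is 16 × √(2/147) = 1.866, and 4/1.866 = 2.143. Power is Φ(2.143 − 1.960) = 57.3%. For 80% power, 252 per group would be needed.

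**Interaction (2 df).** The noncentrality is Σ(d_t − mean d)² / [2 × SD² × (1 − ρ)/n]. The denominator is 2 × 400 × 0.4/147 = 2.177.

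| True difference at T1/T2/T3 | Σ(d_t − mean d)² | Noncentrality | Power at 147 per group |
|---|---|---|---|
| 4/4/4 | 0 | 0 | 5.0% |
| 4/3/2 | 2 | 0.919 | 12.6% |
| 4/2/0 | 8 | 3.675 | 38.5% |
| 4/0/0 | 10.67 | 4.900 | 49.5% |

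For 4/4/4 the rate equals alpha at any sample size. By comparison, if baseline were a level of time (differences 0/4/4/4, 3 df), the interaction would have about 48% power.

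**Simulation check.** In 20,000 simulated trials with complete data, 147 per group and a true difference of 4 at all three times, the rejection rates were 5.2% for the interaction, 57.2% for the T1 contrast and 79.6% for the averaged effect.

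**The case against.** A reader might infer that the plan cannot test efficacy, or that the interaction is its primary test or a gate before the contrasts. The document does not support this. The sentence that mentions the interaction goes on to plan between-group contrasts, treatment condition is a fixed main effect, and nothing makes either conditional on the interaction. Being listed first sets no hierarchy. The Abstract and Measures sections both place the primary endpoint at post-intervention, which points to the T1 contrast. All of this stands.

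The interaction also has a proper use. Whether the group difference changes after T1 bears on the part of the hypothesis about sustained effects, and a durability test should react when benefit fades. The null result also requires the benefit to be equal at all three times, which the hypothesis suggests but does not spell out. These points stand too.

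It can further be said that a formal order of tests is commonly left to a statistical analysis plan, which is not shown. That is fair as far as missing detail goes. It does not remove what the article itself states: it lists, among analyses meant to examine efficacy, a test that cannot detect a constant benefit, and it sets its superiority criterion at one time point while its power figure belongs to an average over three.

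**Conclusion.** The point holds in a limited form. In the stated model the group-by-time interaction tests only whether the adjusted group difference changes after T1, and for a constant 4-point benefit it is significant at the alpha rate. Valid efficacy tests are in the plan and the interaction is not made decisive, so this is not a failure to test efficacy. The weakness is that the Primary analyses section does not connect the decision to the post-intervention endpoint fixed in the Abstract and Measures sections, leaving open tests with about 5%, 57% and 80% power for the same true effect.

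The figures rest on 147 per group with complete data, SD 20, a correlation of 0.6 between all pairs of assessments, two-sided alpha 0.05 (assumed), and a true difference of 4 at T1, T2 and T3. The cancellation of baseline from the interaction depends on none of these numbers, only on the model as described. The sample size arithmetic is not in error: 147 is right for the averaged effect.

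**What to change.** In Primary analyses, state that the adjusted between-group contrast at post-intervention (T1), from the model with group, time, group-by-time and baseline, is the single primary test and is not conditional on the interaction. Naming the full model matters because the listed fixed effects stop at main effects; without the interaction term, the T1 contrast is forced to equal the averaged effect. Use the T2 and T3 contrasts with confidence intervals to judge whether the effect is sustained. Report the interaction only as a description of whether the effect changes over follow-up.

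The wording costs a few sentences, with the same model and data. The downside must be stated openly: at 147 per group the T1 contrast has about 57% power, and even if all 185 per group contributed data it would have about 67%. Reaching 80% would take 252 per group with data, or 252/0.8 = 315 enrolled per group (630 in total, against 370 planned). The power statement in the sample size section should therefore be restated for the T1 contrast, making clear that the present 80% applies to the effect averaged over T1 to T3.

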## Methods and design

### Study design and setting

A multicentre, single-blind parallel RCT, with randomisation at the participant level and stratification by recruitment site. This trial adopts the SPIRIT guidelines for clinical protocols [32], and Fig. 1 outlines the study schema.

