### Recruitment

Eligible participants will be recruited via two methods.

**Direct approach**: Women will be screened for eligibility by cancer clinicians then approached by research assistants (RAs) at the 10 participating health sites (Flinders Medical Centre, South Australia; Royal Brisbane & Women’s Hospital, Queensland; Canberra Hospital, Australian Capital Territory (ACT); National Capital Private Hospital, ACT; Peter MacCallum Cancer Centre, Victoria; Lake Macquarie Private Hospital, New South Wales (NSW); Maitland Private Hospital, NSW; Mater North Sydney Hospital, NSW; Chris O’Brien Lifehouse, NSW; Campbelltown Hospital, NSW). CIs and AIs are affiliated with each of these recruitment sites and research assistants will be employed in each state to facilitate and oversee recruitment at each recruiting hospital. Women who are screened as ineligible will receive standard care as usual.

**Self-selection:** In response to advertisements and promotion through *professional networks* (e.g., McGrath Foundation; BCNA; Cancer Council SA), *breast cancer advocacy groups / agencies* (e.g., Cancer Voices Australia), and *research databases* (e.g., Register4, BCNA Review & Survey group). Participants who self-refer to the study will self-confirm their eligibility as part of the online consent process.

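### Randomisation is stratified by site but the stated mixed model has no site term, so reported standard errors may be slightly too large

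*Protocol article*

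**What the plan says.** Both descriptions of the allocation name site as the stratification factor. The Abstract (Methods) has "with randomisation computer-generated and stratified by site", and Study design and setting has "with randomisation at the participant level and stratification by recruitment site".

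Primary analyses sets out one mixed model for all continuous outcomes:

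- Fixed effects: "the fixed main effects will be treatment condition (intervention, control), and time (post-treatment, 3-month, 6 month".
- Interaction and contrasts: "testing group by time interaction, and estimating and testing differences between groups at time points of interest via linear contrasts".
- Covariate: "with the baseline measure of the outcome entered as a covariate".
- Random part: "A random subject effect will be entered into the model".

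Site is neither a fixed nor a random effect, and no other section says that the analysis adjusts for it.

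There are two recruitment routes. Women are "identified, screened and referred from one of 10 Australian sites, or via self-referral in response to advertisements". Under Recruitment, those who come through a clinic are "approached by research assistants (RAs) at the 10 participating health sites". The article does not say which stratum a self-referred woman enters.

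**The concern.** Stratifying by site balances the arms within each site, which takes between-site differences out of the treatment contrast. A model without site leaves that variance in its error term. The estimate is then more precise than its reported SE suggests, intervals are wider than the design warrants, and some power is given up.

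The article justifies adjusting for baseline by the gain in precision, yet leaves out the only stratification factor it names. There is also a documented reason why referral route might be prognostic. Clinicians screen the women approached at sites, while self-referred women confirm their own eligibility, even though the life-expectancy criterion is defined by the treating clinician's estimate.

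**Working it through.** **Inputs from Sample size and justification:** SD 20, within-subject correlation 0.6, one baseline and three follow-up measures, a 4-point difference, 147 per group, 80% power. **Assumed, because not stated:** two-sided alpha of 0.05, and a site share *s* of the baseline-adjusted variance between 0 and 0.10.

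**Step 1. Reproduce the planned size.** The variance factor for repeated-measures ANCOVA is (1 + 2 × 0.6)/3 − 0.6² = 0.3733. Then n = 2 × (20 × (1.960 + 0.842)/4)² × 0.3733 = 146.5, so 147 per group, with power 80.1%. One-sided 0.05 would give 116, so two-sided 0.05 is the reading that fits. No site term is needed to reach 147.

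**Step 2. Effect of omitting site, averaged over follow-up.** With V = 400 × 0.3733 = 149.3:

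- reported SE = √(2V/147) = 1.425
- true SE under stratified 1:1 allocation = √(2V(1 − s)/147)
- actual alpha = 2[1 − Φ(1.96 × reported SE / true SE)]
- power without site = 1 − Φ((1.96 × reported SE − 4)/true SE)
- power with site = 1 − Φ(1.96 − 4/true SE)

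| s | true SE | SE overstated by | actual alpha | power without site | power with site |
|---|---|---|---|---|---|
| 0 | 1.425 | 0% | 0.0500 | 80.1% | 80.1% |
| 0.01 | 1.418 | 0.5% | 0.0489 | 80.2% | 80.5% |
| 0.02 | 1.411 | 1.0% | 0.0477 | 80.4% | 80.9% |
| 0.05 | 1.389 | 2.6% | 0.0443 | 80.7% | 82.1% |
| 0.10 | 1.352 | 5.4% | 0.0388 | 81.4% | 84.1% |

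**Step 3. The post-treatment contrast alone.** The variance factor is 1 − 0.6² = 0.64, so V = 256 and the reported SE is √(2 × 256/147) = 1.866. The fair comparison is with and without site at the same *s*, because stratification has already lowered the true variance in both. Gains are taken before rounding.

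| s | power without site | power with site | gain (points) |
|---|---|---|---|
| 0 | 57.3% | 57.3% | 0 |
| 0.02 | 57.4% | 58.1% | 0.8 |
| 0.05 | 57.5% | 59.4% | 2.0 |
| 0.10 | 57.7% | 61.8% | 4.1 |

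**Step 4. If site also acts on baseline.** The baseline covariate then absorbs part of the site effect. For a raw site intraclass correlation (ICC) *c*, the within-site variance is 400(1 − c) and the within-site correlation is (0.6 − c)/(1 − c). At c = 0.10 these are 360 and 0.556. The variance factor is 0.395 and the adjusted variance 142.2 against 149.3, so the SE is overstated by √(149.3/142.2) − 1 = 2.5%. For c = 0.01, 0.02 and 0.05 the excess is 0.2%, 0.4% and 1.1%.

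**Step 5. Simulation.** This used 294 women, 4,000 runs per setting, ANCOVA on the mean of the three follow-ups, and assumed permuted blocks of four with near-equal sites. At raw ICC 0.10 with 8 strata, the mean model SE under no effect was 1.425 without site and 1.395 with it. Rejection under no effect was 4.2% and 4.6%; at a 4-point difference it was 79.6% and 80.8%. With 11 strata, rejection at 4 points was 80.9% and 82.0%. This agrees with the formulas within Monte Carlo error.

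**Step 6. How many strata?** Recruitment names 10 sites. The per-site figures in Sample size and justification imply about 8 (370/46 = 8.04; 530/66 = 8.03) and leave no place for self-referred women. The stratification factor therefore cannot be reconstructed from the article.

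**The case against.** The strongest reply is that the effect is conditional, small and in the safe direction. No between-site variance is given, the assumed range is the reviewer's, and zero is possible. Baseline may absorb much of any site effect, as Step 4 shows. All of this stands, and it limits how much weight the point can bear.

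A second reply is that the list of terms may not be complete. Table 2 names baseline covariates that Primary analyses does not mention, and an analysis plan that is not shown may add site. This weakens the point without removing it. Table 2 does not list site either, and the article spells out its model terms. If another document adds site, the published statement needs aligning with it.

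A reader might infer more than the article supports:

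- **That the stratification is wasted.** It is not. The arms stay balanced within site and the estimator's true variance still falls; only the reported SE fails to show it.
- **That the model contains only treatment, time and baseline.** It also has a group-by-time interaction and a random subject effect, although neither accounts for site.
- **That self-referral is an eleventh stratum in the randomisation list.** No section says how self-referred women are stratified.

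**Conclusion.** The omission is plain in the text; its consequence is conditional. If site predicts the outcome beyond baseline, the reported SE is too large by about 0.5-5% for assumed shares of 1-10%, and actual alpha is about 0.049-0.039. About 0.3-3 points of power are forgone for the averaged effect. At post-treatment the loss is about 1-4 points for shares of 2-10%. At a share of zero there is no loss.

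It would be wrong to conclude that type I error is inflated or that the sample size is undermined: the error is conservative, and 147 per group reproduces without site. The lower power of the single post-treatment contrast is a separate matter. It should not add weight here, because a site term would not repair it.

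This is a modest precision and reporting point that is worth correcting because the correction is nearly free. The sizes rest on two-sided 0.05, 147 analysed per group and the assumed site shares.

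**What to change.** Add the stratification factor, coded exactly as in the randomisation, to the mixed model for every continuous outcome. Either a fixed or a random effect would serve, but the choice should be stated. State which stratum self-referred women are randomised in, and reconcile the 10 named sites with the roughly 8 implied by the per-site figures. Set a rule in advance for pooling very small sites. Settling this before unblinding also removes any later choice between adjusted and unadjusted results.

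The cost is a sentence or two and no new data. As fixed effects, 10 sites plus a separate self-referral level, if that is how the randomisation was done, would use 10 of roughly 290 degrees of freedom; fewer strata would use fewer. If site turns out not to be prognostic, that small loss is the only price.
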